## Abstract

**Background:**

Delayed motor development is reported in patients with congenital heart disease (CHD). Exercise is widely used to facilitate motor development and improve motor ability. Exercise for adolescents and adults with CHD has been extensively studied. However, the evidence of exercise for infants with CHD is sparse. This study aims to identify the effect of passive movement and active exercise on motor development within very young CHD infants with cardiac catheterization.

**Methods/Design:**

A prospective and randomized controlled trial will be conducted in very young CHD infants with cardiac catheterization. A total of 147 infants with CHD will be randomized by a 1:1:1 allocation ratio by computer to an exercise intervention group, a home-based intervention group and a control group. The exercise intervention group will receive passive movement and active exercise from experienced physiotherapists in pediatrics three times a week for 12 weeks. The home-based intervention group will receive passive movement and active exercise from their parents or caregivers at home three times a week for 12 weeks. The control group will receive follow up only. The follow-up duration is 20 months. The primary outcome measures are the motor quotient measured by the Peabody Developmental Motor Scales-II. The secondary outcome measures are the Ross score, ventricular function, bone quality, body length, weight, head circumference, upper arm circumference, and adverse events.

**Discussion:**

This study has several important features, including the randomization process, the long follow-up duration, the control group, and the large sample size. The aim of this study is to determine whether 12-week passive movement and active exercise promotes motor development and produces other beneficial effects for very young CHD infants with cardiac catheterization. Therefore, this study will contribute new knowledge regarding the rehabilitation program in very young CHD infants with cardiac catheterization.

**Trial registration:**

Current Controlled Trials ChiCTR-IOR-15005909 (January 31, 2015).

## Background

Congenital heart disease (CHD) is common in infants [1]. The prevalence of CHD was 10.8-26.6‰ [2–4]. With the improvement of echocardiography and medical care, more patients with CHD were underwent cardiac catheterization than ever before. Because of the high success rate, short hospital stay, low morbidity and mortality, cardiac catheterization of CHD is favored over surgery. Cardiac catheterizations have been used to treat neonates with critical congenital heart disease, such as valvar stenosis or atresia [5]. However, patients with CHD frequently exhibit delayed neurodevelopmental function, decreased exercise capacity, impaired exercise performance and lower health-related quality of life.

Pronounced delayed neurodevelopmental function has been observed in children with CHD [6, 7], especially those with cyanotic CHD [7] or catheterization [8] or heart surgery performed with circulatory arrest [9]. Lower exercise function [10, 11], dysfunction in speech and language [12], poor cognitive function [13, 14] and behavior difficulties [8] were also reported in preschool and school-age patients with CHD. The causes of delayed neurodevelopmental function may include hemodynamic defects, long-standing hypoxemia [7], long hospital stay and physical inactivity (for example, prolonged time in strollers and walkers). Inadequate exercise for patients with CHD may lead to cardiovascular complications. Therefore, infants with CHD require a large amount of physical activity to master movement control.

The Cardiac Rehabilitation Program has been studied in adolescents and adults with CHD [15–17]. Exercise is the core component of the cardiac rehabilitation program and is safe, feasible and beneficial. Past studies have documented that exercise increases exercise capacity [10, 18–20], HR recovery following peak exercise [21], respiratory muscle oxygenation and health-related quality of life [15, 16] in adolescents and adults with CHD. In contrast, the use of the cardiac rehabilitation program and clinical research in pediatric populations have been limited [22]. There is only one study of preschool children with CHD, which suggests that the short low-dose intervention program can improve motor ability and delayed motor development [23]. The optimal cardiac rehabilitation program of this unique population is still unknown and needs to be developed.

Performing exercises in infants with CHD remains challenging. To date, there have been few rehabilitation interventions that target infants with CHD. The effect of exercise on motor development in infants with CHD is unknown. Therefore, it is important to identify passive movement and active exercise to facilitate motor development within this population. This paper describes the rationale, design and methodology of a randomized, controlled study being conducted in China.

### Methods/Design

A prospective and randomized controlled trial involving passive movement and active exercise in very young CHD infants with cardiac catheterization will be performed. The aim of the study is to determine:whether passive movement and active exercise beginning at 1 month of corrected age (CA) in infants with CHD improves motor development at 24 months of CA compared with control subjects,the potential benefits of exercise on growth, heart function and bone quality of very young infants with CHD, andthe potential adverse effects related to passive movement and active exercise.

## Study design

The CHD patients with cardiac catheterization will be recruited from and investigated at the Xin Hua Hospital affiliated to the Shanghai Jiao Tong University School of Medicine, Shanghai City, China.

Prior to inclusion, the following information will be obtained for all patients: demographic data (for example, gestational age at birth, birth weight, CA, and gender), medical history (for example, the duration of intensive care unit and hospital stay, and age of cardiac catheterization), heart defect (for example, defect type and size), and type of feeding (for example, breast or artificial feeding). Each patient’s parents will be asked to sign an informed consent form before the patient can participate in the study.

Eligible participants will be randomized by a 1:1:1 allocation ratio by computer either to the exercise intervention group, in which they will receive passive movement and active exercise to promote motor development; the home-based intervention group, in which they will receive passive movement and active exercise from parents or caregivers at home; or the control group, in which they receive follow up only (Fig. 1). The total study duration will be 23 months, which consists of a 3-month intervention and 20-month follow-up period without intervention. All patients will receive the exercise intervention, the home-based intervention, or the control conditions as allocated. All patients will be assessed at 1, 4, 6, 12 and 24 months CA.

**Fig. 1 Fig1:**
[figure not shown]
Flowchart. CHD indicates congenital heart disease; *CA* corrected age, *PDMS-II* Peabody Developmental Motor Scales-II

If the pediatrician evaluating the patient prescribes additional physiotherapy, the patient will receive physiotherapy. The pediatrician will record information if the participant receives other physiotherapy.

## Participants

CHD patients with cardiac catheterization are eligible for the study. Patients who meet the following inclusion criteria will be enrolled:infants with CHD,less than 1 month CA,with a modified Ross score of less than 3 points,availability 5 days a week over a period of 12 weeks,for whom informed parental consent has been provided.

Patients who have any of the following exclusion criteria will be excluded:previous cardiac operation history;a genetic syndrome, respiratory failure, neurological disorder, or arrhythmia;heart failure with a modified Ross score of 3 points or more;significant hemodynamic defects to make exercises inadvisable; orother congenital malformations.

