### Exercise in the supine position

#### Passive range-of-motion exercise

Previous studies have proven that passive range-of-motion exercise with gentle joint compressions is beneficial for weight gain [25, 32] and bone development [26, 33–36] in preterm infants. Consequently, effective passive exercise may be needed in infants with CHD. Each infant will receive passive range-of-motion exercises with gentle joint compressions at the end of each movement. We will perform 10 repetitions of passive range-of-motion exercise on the wrists, elbows, shoulders, ankles, knees, and hips. Each joint flexion/extension motion lasts for 5 s, for a total period of 10 min.

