#### Feet and hand reaching

Goal-directed reaching provides an early intervention strategy to encourage movement in very young infants. Studies have showed that feet and hand reaching training programs were beneficial for the preterm population [27, 28, 37, 38]. Feet and hand reaching using a malleable rubber toy are designed to improve the ability of infants to reach for toys with their feet or hands and promotes the dissociation of the joints. Both feet and hand reaching consists of toy-oriented reaching in three movements by a physiotherapist, as described in a previous study [27, 38]. We will perform 2 repetitions. Each movement lasts for approximately 30 s, for a total period of 6 min.

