### Exercise in the prone position

The prone position is a very important position for infants developing motor development. Young infants are able to take advantage of the prone position to advance their early motor development [39]. The exercises in prone position are designed to develop antigravity movements of the extremities, head control, weight bearing on arm muscles, and strength for sitting. The exercises in the prone position consist of two movements (Table 1) as described in a previous study [29]. Each movement is repeated four times. Each movement lasts for approximately 30 s, for a total period of 4 min.

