## Statistical analysis

The SPSS 20.0 and Microsoft Excel 2013 software will be used for statistical analyses. Demographic data will be described with descriptive statistics, including the mean ± standard deviation (SD). We will use analysis of covariance to compare the primary and secondary outcomes of the three groups. A general linear model will be used to compute mean outcome values adjusted for diagnosis, gender and socioeconomic status (SES), with the group as the fixed factor and diagnosis, gender and SES as covariates. If patients are lost to follow-up, an intention-to-treat analysis will be performed. Statistical significance is set at a p-value less than 0.05.

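### Gestational age at birth is collected but left out of the adjusted model, which costs some precision without biasing the randomised comparison

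*Protocol article*

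**What the plan says.** The protocol article (Participants) admits "infants with CHD,less than 1 month CA". Neither the inclusion nor the exclusion list mentions gestational age. The exclusions name, among others, "a genetic syndrome, respiratory failure, neurological disorder, or arrhythmia", but not prematurity. Entry and every assessment are timed by corrected age, which makes sense only if some preterm infants are expected.

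Study design lists the information obtained before inclusion, beginning with "demographic data (for example, gestational age at birth, birth weight, CA, and gender". Gestational age will therefore be in the data set.

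Statistical analysis does not leave the covariates open. It specifies a general linear model "with the group as the fixed factor and diagnosis, gender and SES as covariates". Gestational age is not among them.

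The rationale for two of the exercise components comes from preterm infants. Passive range-of-motion exercise "is beneficial for weight gain [25, 32] and bone development [26, 33–36] in preterm infants", and "feet and hand reaching training programs were beneficial for the preterm population".

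**The concern.** Birth before term plausibly predicts motor development, growth and bone quality even when visits are scheduled by corrected age. Corrected age aligns the calendar; it does not guarantee that term and preterm infants have the same outcomes at a given visit. A baseline factor that predicts the outcome and is left out of the model has two effects. Its share of the outcome variance stays in the error term and widens the confidence intervals. And if the arms happen to differ in preterm share, the estimate carries that difference uncorrected.

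At stake is precision in a trial of modest size (49 infants per arm, 42 after the planned attrition allowance), and a foreseeable question from readers should the baseline table show unequal gestational age.

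**Working it through.** The plan gives no figure for this point, so there is none to reproduce.

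**Inputs from the article.** 49 infants recruited per arm and 42 needed for analysis; target difference 0.5 SD; two-sided alpha 0.05 (all from Sample size calculation).

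**Assumptions, since the article gives neither.** Preterm share p = 10-40%. Preterm deficit d = 0.5-0.8 SD, in units of the SD within the term or preterm group.

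**1. Variance left in the error term.** For a two-level factor, R² = p(1-p)d² / [1 + p(1-p)d²].
- Low end, p = 0.1 and d = 0.5: 0.0225 / 1.0225 = 0.022.
- High end, p = 0.4 and d = 0.8: 0.1536 / 1.1536 = 0.133.

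Adjustment multiplies the standard error by √(1-R²), that is by 0.989 to 0.931, a reduction of about 1% to 7%.

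**2. What that means for power.** Power of a two-arm t test for 0.5 SD with 42 per arm is 0.62. Replacing 0.5 by 0.5/√(1-R²) gives 0.63 at the low end and 0.68 at the high end. (The article states 80% power for a comparison among three groups. That 0.62 falls short of it is a separate matter and does not affect this point.)

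**3. How often the arms differ in preterm share.** 400,000 simulated trials, three binomial arms of 49, no stratification (the article names no stratification factor), largest minus smallest arm:

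| Preterm share | Gap of at least 10 points | Gap of at least 15 points |
|---|---|---|
| 10% | 28% | 3% |
| 20% | 49% | 14% |
| 30% | 58% | 22% |
| 40% | 62% | 27% |

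**4. What such a gap does to the estimate.** Shift = gap × d.
- 10 points: 0.10 × 0.5 = 0.05 SD to 0.10 × 0.8 = 0.08 SD.
- 15 points: 0.15 × 0.5 = 0.075 SD to 0.15 × 0.8 = 0.12 SD.

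For one pair of arms, the SD of the gap is √[2p(1-p)/49], which is 0.061 at p = 0.1 and 0.099 at p = 0.4. At 1.96 SD the gap is 11.9 and 19.4 points. With d = 0.5 that shifts the estimate by 0.06 to 0.10 SD, and with d = 0.8 by 0.10 to 0.16 SD.

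**5. Does the omission bias the test?** In 20,000 simulated trials with 49 per arm, no treatment effect and no adjustment, the three-group F test rejected in 4.9% (20% preterm, 0.5 SD deficit) and 5.2% (30% preterm, 1 SD deficit). The mean difference between arms was about 0. The test keeps its level.

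**The case against.** The strongest case against acting is that the comparison is valid without the covariate and the gain is small. That stands: type I error stays near 5%, and pairwise power rises by at most about six percentage points under the assumptions above. Corrected age and the exclusion of respiratory failure and neurological disorder may also remove part of the difference between term and preterm infants, so the true deficit could lie below the assumed range. That is fair too, and it would shrink the figures further.

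A reader might go further and infer that a positive result could reflect prematurity and not CHD. The documents do not support this. Every participant has CHD, and concealed computer allocation balances gestational age in expectation. Nor do the cited sources carry the inference. The passive-motion evidence concerns weight and bone, which are secondary outcomes; the reaching evidence covers one component; and the sections on prone, side-lying and supported-sitting exercise name no preterm source population.

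A milder version is that a benefit confined to preterm infants could be reported for all infants with CHD. Nothing in the article rules that out, but nothing in it shows it either. Suppose the effect were 0.8 SD in a 30% preterm subset and nil in term infants. The overall difference would be 0.3 × 0.8 = 0.24 SD, which a two-arm t test detects with power of 19% (42 per arm) or 22% (49 per arm). Such a trial would usually be null. An overall 0.5 SD would need 0.5 / 0.3 = 1.7 SD in the preterm infants.

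The lack of a named stratification factor or subgroup analysis is not held against the plan. A condensed article commonly leaves both to the full protocol or the SAP. The covariate list is different, because the article states it.

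**Conclusion.** The point holds as a modest, low-cost improvement to a stated model. The covariates are fixed without gestational age, although it is collected and is a likely predictor of the motor, growth and bone outcomes. Under an assumed preterm share of 10-40% and an assumed deficit of 0.5-0.8 SD, about 2-13% of outcome variance is left unexplained, and a 10-point chance imbalance shifts a two-arm comparison by 0.05-0.08 SD, at most about a sixth of the 0.5 SD target (0.08 / 0.5 = 0.16). Both ranges rest entirely on those assumptions and would be smaller if few preterm infants enrol or if the deficit at corrected age is slight. The omission is a matter of precision and does not threaten validity. The eligibility criteria need no change.

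**What to change.** In the Statistical analysis section, add gestational age at birth to diagnosis, gender and SES as a covariate for the motor, growth and bone outcomes. Entered in weeks as a linear term, it costs one degree of freedom and uses data already collected. The change should be recorded before any comparison by group is seen, so that it cannot look chosen after the fact.

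If the investigators also want a term/preterm comparison, label it exploratory and keep the overall conclusion on the full randomised comparison. At an assumed 30% preterm share, about 0.7 × 49 = 34 term infants per arm remain (0.7 × 42 = 29 after attrition). Power for 0.5 SD among them is then about 53% (46%), so a null result in term infants would be likely even if the exercises worked.

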## Withdrawal management

The patients with CHD who have any of the following conditions will be allowed or will be asked to withdraw from the study:The patient’s parents require withdrawal.The patient develops heart failure, or respiratory failure, or other serious diseases.The exercises lead to any adverse effects.

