## Control group

Each infant in the control group will receive no training. All participants in the trial will receive health education. This includes group counseling focusing on daily activity and diet. The participants will be asked not to participate in any other rehabilitation treatments.

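### Withdrawal for illness or exercise-related adverse effects is from the study, not only from the exercises, so outcome data can be lost in a way that depends on treatment and prognosis

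*Protocol article*

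**What the plan says.** The Withdrawal management section of the Protocol article lists the conditions under which infants "will be allowed or will be asked to withdraw from the study". Apart from a parental request, there are two kinds of trigger:

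- Illness, possible in any group: "The patient develops heart failure, or respiratory failure, or other serious diseases".
- Harm from the intervention, with no severity threshold: "The exercises lead to any adverse effects".

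The control condition is described under Control group: "Each infant in the control group will receive no training". Study design gives the time course, "which consists of a 3-month intervention and 20-month follow-up period without intervention", with assessments at 1, 4, 6, 12 and 24 months CA. The first aim under Methods/Design is whether exercise "improves motor development at 24 months of CA compared with control subjects".

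The modified Ross score (0 to 12, higher is worse), ventricular function and exercise-related adverse events are secondary outcomes. Statistical analysis promises an intention-to-treat analysis if patients are lost to follow-up. Nothing in the article says that an infant who withdraws under these triggers is still assessed.

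**The concern.** Stopping a treatment and ending observation are different decisions, and the withdrawal section treats them as one. The article does describe stopping the exercises without leaving the study elsewhere: under Intervention group, a session stops if the infant cries. The withdrawal section makes no such distinction.

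Three things are at stake.

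- **Primary comparison.** One trigger arises after randomisation and only where exercise is given. If infants who leave by that route differ in motor development from those who stay, the groups compared at 24 months CA are no longer the groups that were randomised.
- **Cardiac outcomes.** Infants who go into heart failure may not be measured again on the outcomes that would show it, namely the Ross score and ventricular function.
- **Safety aim.** The third aim concerns adverse effects of the exercises. The event is recorded, but its later course may not be.

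An intention-to-treat analysis keeps infants in their allocated group. It cannot supply measurements that were never taken.

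**Working it through.** **Step 1. Which groups each trigger can reach.**

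| Trigger | Exercise group | Home-based group | Control group |
|---|---|---|---|
| Parental request | yes | yes | yes |
| Heart failure, respiratory failure, other serious disease | yes | yes | yes |
| Adverse effect of the exercises | yes | yes | no (no training given) |

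With 1:1:1 allocation, two of the three groups are exposed to the last trigger. Only that trigger is one-sided by construction.

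**Step 2. When it acts.** The exercises run for about 3 months from 1 month CA, so they end at about 4 months CA. The primary aim is at 24 months CA, and 24 − 4 = 20 months. An infant who leaves during the exercise period can miss all four post-baseline assessments (4, 6, 12 and 24 months CA).

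**Step 3. The plan's nearest figure.** The article states no withdrawal rate. Under Sample size calculation it raises 42 per group to 49 for attrition: (49 − 42)/49 = 7/49 = 14.3%. I use this only as an upper limit for the illustration. Nothing here depends on whether 42 is itself correct.

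**Step 4. Illustration of size, on assumed inputs.** Suppose there is no true effect. A share w of an exercise group leaves, being those worst on the characteristic that triggers withdrawal. That characteristic has correlation ρ with the motor quotient, and no control leaves. For a normal outcome in SD units, the mean of those remaining shifts by

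shift = ρ × φ(q)/(1 − w), with q the w-quantile of the standard normal and φ its density.

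For example, at w = 10%, φ(q)/(1 − w) = 0.195, so ρ = 0.5 gives 0.097 SD.

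The approximate two-sided type I error for one exercise–control comparison uses SE = √[1/(49(1 − w)) + 1/49] and equals 1 − Φ(1.96 − shift/SE) + Φ(−1.96 − shift/SE).

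| w | Shift, ρ = 0.3 | Shift, ρ = 0.5 | Share of the 0.5 SD target | Type I error |
|---|---|---|---|---|
| 2% | 0.015 | 0.025 | 3% to 5% | 0.051 to 0.052 |
| 5% | 0.033 | 0.054 | 7% to 11% | 0.053 to 0.058 |
| 10% | 0.058 | 0.097 | 12% to 19% | 0.059 to 0.076 |
| 14.3% | 0.079 | 0.132 | 16% to 26% | 0.066 to 0.096 |

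The mathematical ceiling at ρ = 1 is 0.11, 0.19 and 0.26 SD at 5%, 10% and 14.3%.

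**Step 5. Sensitivity to control withdrawals.** If 5% of controls also leave by the same mechanism, the net shift (ρ 0.3 to 0.5) is 0.026 to 0.043 SD at 10% in the exercise group and 0.046 to 0.077 SD at 14.3%. It is zero at 5%. At 2% it changes sign, to between −0.018 and −0.030 SD. The direction therefore depends on which group loses more infants, and the article does not tell us.

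**The case against.** Several points on the other side are sound and limit what can be claimed.

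- The rule says allowed or asked, so not every affected infant leaves.
- Illness triggers apply in all groups. The article hopes that exercise improves heart function. If it does, more controls than exercised infants could leave for heart failure, and the bias could run against exercise.
- A reader might infer that the worst responders leave the exercise groups and that exercise is thereby favoured. The article does not link an exercise-related adverse effect to a low motor quotient at 24 months CA, so this is an assumption.
- A reader might infer that retained infants can score only 0 to 2 on the Ross score. The threshold "heart failure with a modified Ross score of 3 points or more" is an exclusion criterion under Participants. The withdrawal section sets no score, and an infant found to be in heart failure at a visit can have that score recorded before leaving. The cardiac comparisons are weakened, not disabled.
- The triggering adverse event is recorded under Secondary outcome measures, so the safety aim can still be reported. Only the later course is at risk.
- Intention-to-treat analysis is not made impossible. Infants who leave late contribute earlier assessments, and methods for missing outcomes may properly sit in an analysis plan that is not shown.

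It can also be said that this is a condensed article and that the full protocol may keep withdrawn infants in follow-up. That would settle the matter if so. But the article does more than omit a detail: it states a rule, and the rule as stated ends participation in the study. No later analysis recovers data that were not collected.

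**Conclusion.** The concern holds. As written, the rule can end outcome collection for reasons related to treatment and prognosis, and one of its triggers cannot occur in controls. This can bias the 24-month CA comparison, reduces the ability of the Ross and ventricular function comparisons to show deterioration, and can leave the course of exercise-related adverse events unobserved.

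The direction and size are unknown because the article gives neither a withdrawal rate nor the prognosis of those withdrawn. Under the assumptions shown (5% to 14% of an exercise group and no controls withdrawn, correlation 0.3 to 0.5), the shift is 0.03 to 0.13 SD, with type I error for one comparison between about 0.05 and 0.10. With about 2% withdrawn it is negligible. The stronger conclusion, that the trial is biased in favour of exercise, is not supported.

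**What to change.** Divide the withdrawal section into two parts.

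1. **Stopping the study exercises.** Leave the clinical triggers unchanged, but make them reasons for stopping the exercises. When the exercises should stop is a clinical matter and is not judged here.
2. **Ending follow-up.** Only when parents withdraw consent to follow-up.

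State that every infant stays in the allocated group and is assessed at the scheduled 4, 6, 12 and 24 months CA visits where consent and the infant's condition allow, and that the reason and date of stopping the exercises are recorded. The proviso on condition is needed because some infants may be too ill to assess.

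The cost is a short amendment with matching consent wording, plus attendance at a few visits that are already scheduled. The planned sample size does not change. For infants kept in follow-up, the selection created by this rule disappears. Recruitment is already under way, so the change should be made soon: assessments that are missed cannot be recovered.
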